***Derivation of variables***

Age will be defined by the age that the patient was on the date of their operative procedure. The number of patients undergoing surgery will be categorised into 5-year age epochs e.g. Age 0-4, 5-9, 10-14…. until 90+. The lifetime risk will be calculated and repeated for consecutive years that we have data available, this has been done in previous papers assessing the lifetime risk of diabetes(9, 10).

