**Life tables**

We will report the lifetime risk of surgery using life tables, this is considered a more accurate method for lifetime risk in comparison with cumulative risk as it considers the competing risk of death in the population(11). This will be calculated with a 95% confidence interval. The lifetables method has been used to calculate the lifetime risk of diabetes(9, 10). To calculate lifetime risk via the lifetable method we need to find the incident rate, mortality rate of those that have had surgery and the mortality rate for those who have not had surgery in each 5-year epoch. This can be done using the following equations(9):

[figure not shown]

[figure not shown]

Where
[figure not shown]
 is all-cause mortality,
[figure not shown]
 is the age-specific morality rate for those who have had surgery,
[figure not shown]
 is the age-specific morality rates for those that have not had surgery, Relative risk (RR) is the age-specific relative risk of mortality for those who have had surgery and
[figure not shown]
 is the age-specific prevalence of surgery.

The incident and mortality rates can then be used to find out the probability that a patient will transition from the state of not having surgery to having surgery or death and from having surgery to death, this is shown in the following equations(9):

Probability of transitioning from no surgery to death:

[figure not shown]

Probability of transitioning from no surgery to surgery:

[figure not shown]

Probability of transitioning from surgery to death:

[figure not shown]

Where IR is the age-specific incident rate of surgery and L is a period of time (five years). This will allow us to calculate the probability that a person aged x who has not had surgery will have surgery before reaching age x+1 or will die without having surgery before reaching age x+1. This can be applied to a hypothetical cohort to estimate the number of individuals in the population undergoing surgery at each 5-year epoch.

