**Cumulative risk**

Cumulative risk can be used to estimate the lifetime risk of having surgery. This is calculated using the following equation(11):

[figure not shown]

Where P is the cumulative risk until age
[figure not shown]
, C_x_ is the total number of surgeries in age group
[figure not shown]
 and n_x_ is the number of person-years of age group
[figure not shown]
. This is multiplied by 5 as 5-year epochs are used. This will be calculated with a 95% confidence interval.

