**Appendix 2**

### *The Life Table Method*

We calculated lifetime risk for both men and women in a sex-differentiated fashion because the life table method does not allow combined analyses. The incident rate of surgery in person-years was calculated for each 5-year epoch. We calculated surgical mortality rate and the all-cause mortality rate in person-years for each 5-year epoch.

The probability of no longer being alive and surgery free was calculated using equation 1^4^:

$$\lambda_{i}=r_{i}+m_{i}-s_{i}$$

Where $r_{i}$ is the incident rate of surgery in person years, $m_{i}$ is the all-cause mortality rate and $s_{i}$ is the surgical mortality rate. The probability of being alive and without previous surgery at age i was calculated using equation 2^4^:

$$S_{0}(i)=exp[-5\sum_{x=5}^{i} \lambda_{i}]$$

This was multiplied by 5 due to 5-year epochs being used.

Lifetime risk at age *i* was then calculated using equation 3^4^:

$${l_{i}=S}_{0}(i)\times r_{i} \times\frac{1-exp(-{5(\lambda}_{i}))}{\lambda_{i}}$$

The lifetime risk for period *y* (e.g. from 0-90) is calculated using equation 4^4^:

$$LR(y)= \sum_{i=0}^{90} l_{i}(y)$$

*Cumulative Lifetime Incidence*

Cumulative incidence was also used to estimate the lifetime risk of surgery, it was possible to calculate the overall cumulative lifetime incidence of first and all surgery as this method does not rely on mortality rates so male and female data can be combined. We calculated this using equation 6^10^:

$$P=1-exp(-5\sum_{x=5}^{i} r_{i})$$

Where P was the cumulative incidence until age i and $r_{i}$ is the incidence rate in person-years. This was multiplied by 5 as we used 5-year epochs.

**Supplementary figure 1:** Men (blue line) compared to women (red line) cumulative lifetime incidence of first surgery based on the years 2016-19. Error bars are the 95% CIs.

**Supplementary figure 2:** Men (blue line) compared to women (red line) cumulative lifetime incidence of all surgery based on the years 2016-19. Error bars are the 95% CIs.

**Supplementary figure 3:** Pre-pandemic (blue line) compared to the pandemic (red line) lifetime risk of all surgery for men and women (Error bars are 95% CIs). The pre-pandemic period was based on data from 2016-19 and the pandemic period was based on data from 2020. This was calculated using the life table method.

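### The life-table method gives the open 90+ band a width of exactly five years, so the result is neither risk to age 90 nor lifetime risk; the effect on risk from birth is small

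*SAP*

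**What the plan says.** **Age bands.** Under Derivation of variables: "The number of patients undergoing surgery will be categorised into 5-year age epochs e.g. Age 0-4, 5-9, 10-14…. until 90", followed by a plus sign, so the last band is open. Sample tables 1 to 3 each have 19 rows, from 0-4 to 90+.

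**Life-table method (Appendix 2, repeated in the change log).** With r the surgery rate, m all-cause mortality and s surgical mortality, equation 1 sets λ = r + m − s. Equation 2 gives the surgery-free survival S0(i), and is followed by "This was multiplied by 5 due to 5-year epochs being used". Equation 3 gives the contribution of band i as S0(i) × r × (1 − exp(−5λ))/λ, with the same 5 for every i. Equation 4 adds the contributions from i = 0 to i = 90. On the span covered, the text says only: "The lifetime risk for period *y* (e.g. from 0-90) is calculated using equation 4".

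**Cumulative method.** Equation 6 also uses five years throughout ("This was multiplied by 5 as we used 5-year epochs"), as does the main-text section Cumulative risk ("This is multiplied by 5 as 5-year epochs are used"). Both are defined as running until a stated age.

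No section gives another width or a closing term for 90+, or says that risk is deliberately cut at 95.

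**The concern.** Rates for an open band are averages over everyone aged 90 or more. Equation 3 applies them as if the band closed at 95, and then discards the people who are still alive and surgery-free. They remain at risk of a first operation until death.

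The primary objective is the population lifetime risk of surgery, which the Background defines over a whole lifetime. The sum in equation 4 is not that quantity. It is not risk to age 90 either, because such a risk would leave the last term out. Nor is it a clean risk to 95, because rates averaged over all ages above 90 are applied to the first five years only. The shortfall is deterministic, so the planned confidence intervals do not cover it.

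**Working it through.** The SAP states no rates and no lifetime-risk value, so there is no figure to reproduce. All rates below are assumptions.

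**1. Which band is i = 90?** From 0 to 90 in steps of five there are 90/5 + 1 = 19 terms, which matches the 19 table rows. The last term is therefore the 90+ band.

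**2. Share lost.** For someone alive and surgery-free at 90:
- as written: r(1 − exp(−5λ))/λ
- open band, integrated to infinity: r/λ
- share lost: exp(−5λ), which is above zero for any finite λ, so the bias is always downward.

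| r | m − s | λ | As written | Open band | Share lost |
|---|---|---|---|---|---|
| 0.03 | 0.16 | 0.19 | 9.7% | 15.8% | exp(−0.95) = 38.7% |
| 0.05 | 0.20 | 0.25 | 14.3% | 20.0% | exp(−1.25) = 28.7% |
| 0.08 | 0.25 | 0.33 | 19.6% | 24.2% | exp(−1.65) = 19.2% |

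With wider assumptions (r = 0.02 to 0.20, m − s = 0.15 to 0.30) the share lost runs from 8% to 43%.

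**3. Effect on risk from birth.** This is the gap in step 2 multiplied by S0(90), taken here as the probability of being alive and surgery-free on reaching 90.
- Central rates, S0(90) = 6%: 5.73 points × 0.06 = 0.34 points.
- Smallest gap in the range (r = 0.03, m − s = 0.25), S0(90) = 3%: 2.64 × 0.03 = 0.08 points.
- Largest gap (r = 0.08, m − s = 0.16), S0(90) = 10%: 10.04 × 0.10 = 1.00 point.

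In full illustrative life tables S0(90) is derived rather than assumed. These used Gompertz mortality, surgery rates rising with age at five overall levels, and 90+ mortality of 0.15 to 0.30. S0(90) fell between about 0.0001 and 0.08, and risk from birth changed by 0.00 to 0.21 points.

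**4. Rates that vary within 90+.** Three scenarios had mortality rising, and surgery rates constant or falling, above age 90. Band-average rates among the surgery-free were then put into each form.

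| True remaining risk | r/λ | Five-year form | True risk to 95 |
|---|---|---|---|
| 0.194 | 0.194 | 0.141 | 0.151 |
| 0.299 | 0.299 | 0.229 | 0.252 |
| 0.246 | 0.246 | 0.195 | 0.219 |

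The five-year form falls below even the true risk to 95.

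**5. Cumulative method.** At r = 0.10 and m − s = 0.20, equation 6 applied to the 90+ band alone gives 1 − exp(−0.5) = 39.3%, above the life-table value of 0.10/0.30 = 33.3%. Letting the width grow without limit drives it to 100%. It ignores death, so an open band has no finite counterpart there.

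**The case against.** **The indexing could be read otherwise.** Equation 2 sums from x = 5. If the index marks a band's upper age, i = 90 is the 85-89 band, and equation 4 would agree with its 0-90 example. But equation 4 starts at i = 0, which has no meaning on that reading, and its 19 terms match the 19 rows. The lower-age reading fits better, though not perfectly: taken literally, equation 2 then omits the 0-4 band and includes the 90+ exit rate in S0(90). That is a separate defect. It is why the working defines S0(90) as survival to exact age 90.

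**The 14.3% against 20.0% contrast is conditional.** It applies to someone who reaches 90 surgery-free, and no equation in the SAP divides by S0(90). A reader might infer that the 90+ row of Sample table 3 will be far too low. The SAP does not say whether those rows are cumulative from birth, band contributions or remaining risk. If they are cumulative, the 90+ row is the headline figure and barely moves.

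**A reader might infer that every lifetime-risk formula is understated.** That does not hold for the cumulative method, which ignores death and runs to a finite age (step 5). The main-text formulas are not visible, and the change log amends the life-table method set out there.

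**A reader might infer that the pandemic comparison is distorted.** This is not established. If r falls from 0.05 to 0.035 with m − s = 0.20, the share lost rises from 28.7% to exp(−1.175) = 30.9%. The conditional loss, however, falls from 5.7 to 0.035/0.235 × 30.9% = 4.6 points. The net effect on risk from birth also depends on S0(90) in each period, which the SAP does not give.

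**Closing the band is not the only valid choice.** This stands: a risk to a named age, labelled as such, is equally sound.

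**Conclusion.** The error holds for the life-table method, which is the primary one. An open band is given a five-year width with no closing rule, so the estimate matches no stated age span and is biased downward. This rests on reading i = 90 as the 90+ band, which the count of terms and rows supports.

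Over the main assumed range, 19% to 39% of the 90+ contribution is lost. Because few people are likely to be alive and surgery-free at 90, risk from birth moves by roughly 0 to 0.2 points in the illustrative tables. About 1 point requires S0(90) as high as 10%. Severity is minor. For the cumulative method there is no claim of understatement, only an upper age that the five-year width leaves undefined.

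**What to change.** In Appendix 2 and the change log, choose one of the following:
- **Close the band.** Apply equation 3 to bands 0-4 through 85-89, and use S0(90) × r/λ with the 90+ rates for the last band. State that S0(90) is the probability of being alive and surgery-free on reaching age 90.
- **Truncate.** Drop the 90+ term and label the result *risk to age 90*.

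For equation 6, stop the sum at 85-89 and label it *cumulative incidence to age 90*.

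The cost is about one line of text and one of code, with no new data. Closing the band assumes constant rates above 90, and the two methods then cover different spans, which their labels must show. Truncating keeps the spans equal but gives up the claim to a whole-lifetime figure. Removing the 90+ term makes the cumulative figure slightly lower.

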***Impact of COVID-19 Pandemic***

We will consider COVID-19 as an exposure and calculate its impact on the lifetime risk of having surgery. The impact of the COVID-19 pandemic on the lifetime risk of surgery will be investigated by assessing for any difference in lifetime risk in the specified time-period for pre-pandemic and pandemic. We will do this by generating the five-year epochs for the pre-pandemic period and then for the pandemic period and comparing the two. To investigate for a significant statistical difference between the lifetime risk of surgery in the pre-pandemic period and the pandemic period we will use two methods. The first test will involve using 95% confidence intervals(12). If the 95% confidence intervals for the lifetime risk of surgery in the pre-pandemic period does not overlap with the 95% confidence intervals in the pandemic period or the 95% uncertainty interval for relative percentage change does not include 0 then there will be a statistically significant difference in the lifetime risk of surgery between the pre-pandemic and pandemic periods(12). The second test will be a T-test, a P-value 0.05 will be considered statistically significant.

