**Sample table 3: Lifetime Risk**

|  | **Pre-Pandemic** | | **Pandemic** | |
| --- | --- | --- | --- | --- |
| **Age groups (years)** | **Lifetime risk (%)** | **95% CI** | **Lifetime risk (%)** | **95% CI** |
| **0-4** |  |  |  |  |
| **5-9** |  |  |  |  |
| **10-14** |  |  |  |  |
| **15-19** |  |  |  |  |
| **20-24** |  |  |  |  |
| **25-29** |  |  |  |  |
| **30-34** |  |  |  |  |
| **35-39** |  |  |  |  |
| **40-44** |  |  |  |  |
| **45-49** |  |  |  |  |
| **50-54** |  |  |  |  |
| **55-59** |  |  |  |  |
| **60-64** |  |  |  |  |
| **65-69** |  |  |  |  |
| **70-74** |  |  |  |  |
| **75-79** |  |  |  |  |
| **80-84** |  |  |  |  |
| **85-89** |  |  |  |  |
| **90+** |  |  |  |  |

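### Equation 3 labels one age band's contribution as the lifetime risk at age i; if it fills Sample table 3, it understates lifetime risk and can rise when surgery falls

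*SAP*

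**What the plan says.** Appendix 2, The Life Table Method, gives four equations, which the change log repeats. In plain notation:

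- Equation 1: λ_i = r_i + m_i − s_i, from the surgery rate, all-cause mortality and surgical mortality.
- Equation 2: S_0(i), the probability of being alive and surgery-free at age i, is the exponential of −5 times a sum of λ.
- Equation 3: l_i = S_0(i) × r_i × (1 − exp(−5λ_i))/λ_i. The text calls l_i the lifetime risk at age i, which "was then calculated using equation 3".
- Equation 4: LR(y) is the sum of l_i over ages 0 to 90, and is called the lifetime risk for the period.

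"Sample table 3: Lifetime Risk" has one row for each of 19 age groups. For the pre-pandemic and the pandemic period it asks for a lifetime risk in per cent with a 95% CI.

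The section Impact of COVID-19 Pandemic describes the comparison as "generating the five-year epochs for the pre-pandemic period and then for the pandemic period and comparing the two". It judges significance by CI overlap or by an interval for relative change, and by a t-test.

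**The concern.** Equations 3 and 4 cannot both deliver a lifetime risk, because the second is the sum of the first. A term of that sum is the chance that surgery falls inside one band. It is neither the risk accumulated up to age i nor the risk still ahead of a surgery-free person of age i, and a reader of a lifetime-risk-by-age table would expect one of those.

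The label matters because Sample table 3 uses the same term and the same age index, and Appendix 2 gives no other age-indexed life-table quantity under that name. An analyst filling the table from the equations would naturally enter l_i.

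Two things would follow. The entries would be far too small to be read as lifetime risks. They would also respond to two opposing forces when surgery falls: r_i drops, but S_0(i) rises because more people reach age i without surgery. At older ages the second force can win, and the table would then show a higher lifetime risk in a period when fewer operations were done at every age.

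**Working it through.** **Inputs.** The SAP states no lifetime risk and no age-specific rate, so there is no figure of its own to reproduce. Equations 1, 3 and 4 and the 19 bands come from the SAP. Everything else is assumed:

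- Surgery rates r averaging 0.03 per person-year. By band from 0-4 to 90+: 0.0132, 0.0132, 0.0106, 0.0158, 0.0211, 0.0238, 0.0238, 0.0211, 0.0211, 0.0238, 0.0264, 0.0317, 0.0369, 0.0449, 0.0528, 0.0581, 0.0554, 0.0449, 0.0317.
- Mortality m from 0.0001 in childhood to 0.22 at 90+, and s = 0.005 × r.
- A pandemic factor k that multiplies every r_i and s_i.
- S_0(i) taken at the start of band i, that is, summed over the bands before i.

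**When l_i rises.** Let H_i be the cumulative surgery hazard before age i, 5 × the sum of r over earlier bands. Mortality cancels from the ratio of S_0 between periods. Ignoring the small within-band factor,

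l_i(k) / l_i(1) ≈ k × exp((1 − k) × H_i),

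which exceeds 1 when H_i > −ln(k)/(1 − k). The matching cumulative risk is 1 − exp(−H_i):

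| Fall in surgery | k | Threshold H_i | Cumulative risk before age i |
|---|---|---|---|
| 10% | 0.9 | 1.05 | 65% |
| 30% | 0.7 | 1.19 | 70% |
| 50% | 0.5 | 1.39 | 75% |

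**Numbers put in, k = 0.7.** The twelve rates before age 60 sum to 0.2456, so H_60 = 5 × 0.2456 = 1.23, just above 1.19. The ratio is about 0.7 × exp(0.3 × 1.228) = 1.01. Before age 70 the sum is 0.3274, so H_70 = 1.64 and the ratio is about 0.7 × exp(0.3 × 1.637) = 1.14.

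**Full calculation, k = 0.7** (pre-pandemic to pandemic, %):

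| Band | l_i | Running sum through band | Remaining risk from start of band |
|---|---|---|---|
| 55-59 | 4.72 to 4.66 | 69.6 to 56.6 | 66.5 to 54.7 |
| 60-64 | 4.49 to 4.66 | 74.1 to 61.3 | 62.6 to 50.9 |
| 70-74 | 3.57 to 4.23 | 81.9 to 70.2 | 51.2 to 40.3 |
| 80-84 | 1.43 to 2.00 | 85.9 to 75.5 | 31.1 to 23.3 |
| Total (equation 4) | | 86.6 to 76.6 | |

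The exact ratio at 70-74 is 4.23/3.57 = 1.18, close to the approximate 1.14. l_i rises in all seven bands from 60-64 to 90+. The running sum and the remaining risk fall in all 19 bands.

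**Sensitivity to the rate level.**

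- At a mean r of 0.01 or below, with S_0 at band start, there is no reversal.
- At 0.02 and above it appears for each k tried (0.9, 0.7, 0.5), under all four readings of equation 2 tried: bands before i, bands through i, the sum from x = 5 as printed, and the literal index.
- The only volume in the SAP is 5.1 million people a year. Over an assumed 65 million that is 5.1/65 = 0.078 per person-year. At that rate with k = 0.7, l_i rises in all 13 bands from age 30 (70-74: 0.57% to 1.55%) while the total falls from 98.7% to 96.4%. This rate counts everyone operated on in a year, so it speaks to the all-surgery analysis and not to first surgery.

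**The case against.** No sentence says that equation 3 fills Sample table 3. The sample tables suit the transition-probability method in the main text and have no split by sex, which Appendix 2 adopts. Sample table 1 already has a separate column for the proportion of the hypothetical cohort undergoing surgery in each band, which suggests that per-band quantities and lifetime risk were meant to be distinct. Equation 4 gives 0-90 only as an example range, so running or remaining sums would also fit the text. All this stands: that l_i goes into the table is an inference. But nothing in the SAP names an alternative, so the inference remains the natural one.

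A reader might go further and infer that the headline pandemic test would give the wrong direction. The documents do not support that. In the comparison sentence, the two things compared can be the two periods as a whole, and the significance rule speaks of the lifetime risk in each period. On that reading the equation 4 total is tested, and with S_0 at band start it falls when surgery falls.

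A reader might also infer that a spurious increase would be declared statistically significant. No confidence interval was computed, so this is not shown.

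The captions of Supplementary figures 3 and 4 do not say which quantity is plotted and settle nothing either way.

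**Conclusion.** The label is wrong on the SAP's own equations: l_i is a term of the lifetime risk and not a lifetime risk. That part needs no assumption. The consequences are conditional.

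- **If l_i fills Sample table 3,** it understates lifetime risk by age. It is below the remaining risk in every band, and below the running sum in every band after the first, where the two coincide.
- **Reversal at older ages** additionally needs a cumulative surgery hazard before that age of about 1.19 for a 30% fall, or roughly 70% cumulative risk. The SAP gives no age-specific rates from which to tell whether first surgery reaches this.
- **The period comparison** is affected only if it is made band by band.

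The percentages above are illustrations on assumed rates and mortality. The statement about the total rests on S_0 at band start. If equation 2 sums through band i from the first band, even the total can rise at high rates (77.2% to 79.0% at 0.078 and k = 0.7), but that is a separate problem with equation 2.

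This should be corrected. It does not show that the headline comparison is wrong.

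**What to change.** - In Appendix 2, rename l_i the contribution of band i to lifetime risk.
- State what fills Sample table 3: either the running sum of l_k through band i, or the remaining risk for a surgery-free person at age i (the sum of l_k for k ≥ i, divided by S_0 at the start of band i). Name the choice in the column heading.
- In Impact of COVID-19 Pandemic, state that the periods are compared on the equation 4 total and, by age, on r_i or the chosen cumulative or remaining risk, and not on l_i.

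The cost is one relabelled quantity and a few sentences. The point estimates are sums of terms already calculated and need no new data; the 95% CIs must be those of the chosen quantity.

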***Participants and data collection***

All patients, of any age, identified as undergoing surgery using HES-APC in England between 1^st^ April 2015 and 31^st^ August 2020 will be included. Surgery will be defined using the assigned Office of Population Census and Surveys Version 4 (OPCS-4) codes for hospital procedures. Surgical procedures will be identified by using a predetermined list of OPCS-4 codes(1). The number of patients undergoing surgery will be categorised into 5-year age bands. Population estimates will be found using national life tables released from the ONS, this again will be categorised into aged-specific 5-year age bands(8).

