***Statistical Analysis***

There are two validated methods to measure lifetime risk – life tables and cumulative risk. We will calculate the lifetime risk of surgery using both methods, with life table’s being the primary method.

We will report the total number of patients undergoing surgery, as defined using the OPCS-4 codes, in the time frame assessed. This data will be categorised by 5-year epochs. We will then divide the total number of patients undergoing surgery for each 5-year epoch by the total population in that 5-year epoch using population estimates from ONS data. This will give us the age-specific incidence rates of surgery per head of the population.

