**Supplementary figure 4:** Pre-pandemic (blue line) compared to the pandemic (red line) lifetime risk of first surgery for men and women (Error bars are 95% CIs). The pre-pandemic period was based on data from 2016-19 and the pandemic period was based on data from 2020. This was calculated using the life table method.

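### Lifetime risk of 'first surgery' rests on records that begin in April 2015, so in 2016-19 'first' can only mean first recorded since then, and the level of the estimate is unsafe

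*SAP*

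**What the plan says.** The SAP (Participants and data collection) includes patients "identified as undergoing surgery using HES-APC in England between 1^st^ April 2015 and 31^st^ August 2020 will be included". Study design and setting gives the same window, and no other source of surgery records is described.

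Appendix 2 then reports first surgery and all surgery as separate series. Under Cumulative Lifetime Incidence it refers to the "overall cumulative lifetime incidence of first and all surgery", and Supplementary figure 1 shows "cumulative lifetime incidence of first surgery based on the years 2016-19". Supplementary figure 4 gives first surgery by the life-table method, which the Statistical Analysis section makes the primary method. On the periods, the captions state: "The pre-pandemic period was based on data from 2016-19 and the pandemic period was based on data from 2020".

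Equation 2 is introduced in these words: "The probability of being alive and without previous surgery at age i was calculated using equation 2". The Statistical Analysis section forms the age-specific rate by dividing the number of patients "by the total population in that 5-year epoch using population estimates from ONS data". Appendix 2 restates the rate in person-years and does not restrict the at-risk group.

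The SAP does not define first surgery, gives no look-back or washout, and mentions no correction for operations before April 2015.

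**The concern.** Equations 1-4 and 6 give the probability of ever having an operation only if r_i is the rate of first-ever surgery. S_0(i) refers to a whole life up to age i, which for the oldest band is about 90 years. The data can look back less than five years from any operation in 2016-19. A 70-year-old operated on in 1990, 2005 and 2017 would enter as a first case in 2017.

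The primary objective is the population lifetime risk of surgery, and the Background describes lifetime risk as the risk that an event occurs over an average lifetime. The all-surgery series counts repeat operations, so the first-surgery series is the one that reads as a probability of ever having surgery. If adult 'first' rates are partly rates of repeat surgery after a quiet spell, that probability is mislabelled. The problem does not depend on the pandemic comparison, and a short common look-back would keep more of it.

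**Working it through.** **Look-back available.** From 1 April 2015 to 1 January 2016 is 9 months; to 31 December 2019 it is 57 months. Calendar years are assumed. The whole window, to 31 August 2020, is 65 months, so no other reading of the period gives a lifetime history.

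**No stated figure to reproduce.** The SAP gives no rate or lifetime-risk value. The effect therefore has to be shown on an assumed population. The Background's 5.1 million people a year, over an assumed 56-67 million, is 7.6-9.1% a year (5.1/67 to 5.1/56). Annual rates h of 3-8% were used.

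**Model 1, clustering by frailty.** Each person's rate is z × h, with z gamma-distributed, mean 1 and shape k; small k means strong clustering. With look-back t and the total population as denominator, the apparent first-surgery rate is h(1 + ht/k)^-(k+1), averaged over t = 0.75 to 4.75 years.

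Hand check with equation 6, which needs no mortality (constant h = 5%, ages 0-90):
- k = 1, true risk: 1 - 1/(1 + 0.05 × 90) = 1 - 1/5.5 = 81.8%.
- k = 1, as planned: average of (1 + 0.05t)^-2 = 20 × (1/1.0375 - 1/1.2375)/4 = 0.779. The rate is 0.05 × 0.779 = 0.0389, and 1 - exp(-90 × 0.0389) = 97.0%. Error: +15.2 points.
- No clustering, true risk: 1 - exp(-4.5) = 98.9%.
- No clustering, as planned: rate = (exp(-0.0375) - exp(-0.2375))/4 = 0.0436, and 1 - exp(-90 × 0.0436) = 98.0%. Error: -0.9 points.

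Life-table results (equations 1-4, assumed Gompertz mortality, s_i = 0, summed from age 0 although the printed sum in equation 2 starts at x = 5):

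| Annual rate, shape k | True | As planned, 2016-19 | Error (points) |
|---|---|---|---|
| 3%, 0.3 | 46.9% | 79.1% | +32.2 |
| 3%, 1 | 68.2% | 83.4% | +15.2 |
| 5%, 0.5 | 65.0% | 91.0% | +26.0 |
| 5%, 1 | 77.9% | 92.7% | +14.8 |
| 8%, 0.3 | 59.5% | 94.0% | +34.5 |
| 8%, 1 | 84.8% | 97.0% | +12.2 |

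With weaker clustering the error shrinks. At 3% it is about +8.5, +5 and +3 points at shapes 2, 3 and 5; at 8% it is about +5, +2.5 and +1. At shape 10 it is near 0 at both rates, and with no clustering it is about -0.5 to -2.

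**Model 2, a higher rate after a first operation.** First-surgery rate 0.01 a year, rising with age; the rate in those already operated on is a multiple of it. True life-table risk is 50.0%.

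| Rate ratio | Total-population denominator | Recently operated people removed |
|---|---|---|
| 1 | 49.1% | 50.0% |
| 1.5 | 53.2% | 54.2% |
| 2 | 56.8% | 58.0% |
| 3 | 62.8% | 64.4% |

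**Effect of look-back length (model 2).** At look-backs of 0.75, 2.75 and 4.75 years:
- Ratio 1, total population: 49.7%, 49.1%, 48.4%. Ratio 1, matched denominator: 50.0% each time.
- Ratio 2, total population: 58.1%, 56.7%, 55.4%. Ratio 2, matched denominator: 58.5%, 58.0%, 57.6%.

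With the total population as denominator the estimate falls as look-back grows even without clustering, so the fall is ambiguous. With the matched denominator it falls only when there is clustering.

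**The case against.** The strongest reply is that the direction is not settled by the documents. Overstatement requires people with earlier operations to have a higher rate of further surgery than people never operated on. The SAP gives no figure for this, and its total-population denominator pulls the estimate down. This stands: a reader might infer that the lifetime risk is certainly overstated, or that the reported figure is an upper bound, and neither follows. An excess of 12 to 35 points arises only at gamma shapes of 0.3 to 1.

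A reader might also infer that the distortion grows steadily with age. It need not. In model 1 at 8% and shape 1, the gap between the cumulative curves peaks near age 50 (13.7 points) and narrows to about 12 by age 90; at shapes 2 to 5 the estimate is too low at age 10.

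Nor does the SAP call first surgery its primary or headline result. The objective and outcome say only surgery, and Supplementary figure 1 uses the secondary method.

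Finally, no rule in the SAP says that people without a recorded operation are treated as never operated on, and the extract might hold earlier records. But on the data described, the two groups cannot be told apart. None of these replies closes the gap between a whole-life definition and less than five years of history.

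**Conclusion.** The point holds as a mismatch between what the first-surgery series is said to measure and what the described records can show. On those records, first surgery in 2016-19 can only mean first recorded since 1 April 2015. The lifetime figure is expected to exceed the risk of first-ever surgery if repeat surgery clusters in the same people, by an amount the SAP does not allow one to fix. The range of about -2 to +35 points rests on assumed annual rates of 3-8%, gamma frailty from none to strong, Gompertz mortality, s_i = 0 and calendar years. This should be settled before any lifetime figure for first surgery is presented.

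**What to change.** 1. Define the outcome and relabel it 'first recorded operation since 1 April 2015'. Do not present it as lifetime risk of first-ever surgery. State that it probably overstates that risk if repeat surgery clusters, without calling it a guaranteed upper bound.
2. Add a sensitivity analysis in 2019, where every operation has at least 45 months of history: recompute rates and lifetime risk with look-back cut to 9, 21, 33 and 45 months, by age band and sex, and report all four values. The 2016-19 base can stay.
3. Remove people with a recorded operation in the look-back window from the denominator too, so that numerator and at-risk group match. In model 2 this removes the downward pull and makes the look-back table readable. It does not cure the main problem: under clustering it raises the estimate slightly (56.8% to 58.0% at ratio 2).
4. If the extract already holds earlier HES records, use them to flag prior surgery and extend the table.

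The cost is a less ambitious claim and a small amount of extra analysis on data already held. The table shows how far the estimate still moves with look-back; it does not recover the lifetime value.
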